## Abstract

**Background:**

Primary dysmenorrhea (PD) is one of the most common health complaints all over the world, specifically among young females. Acupuncture has been employed to relieve the pain-based symptoms and to avoid the side effects of conventional medication, and wrist-ankle acupuncture (WAA) has confirmed analgesic efficacy for various types of pain. The aim of this study is to evaluate the immediate analgesia effect of WAA on PD of young females.

**Methods/design:**

This study will carry out a randomized parallel controlled single-blind trial to observe the immediate analgesia effect of WAA in PD of young females. Sixty participants who meet inclusion criteria will be recruited from September 2016 to September 2017 in Changhai hospital of China. They are randomly assigned to WAA therapy or sham acupuncture groups (30 patients for each group), and then receive real or sham acupuncture treatment, respectively. In this trial, the primary outcome measure is simple form of McGill pain questionnaire (SF-MPQ), while expectation and treatment credibility scale (ETCS), safety assessment, the COX menstrual symptom scale (CMSS), questionnaire about the feeling of being punctured are included in the secondary outcomes.

**Discussion:**

This trial will be the first study protocol designed to evaluate the immediate analgesia effect of WAA in PD of young females. The strengths in methodology, including rigorous randomized, sham-controlled, participants-blinded and assessors-blinded, will guarantee the quality of this study. WAA doesn’t require any needling sensation, so non-penetrating sham acupuncture can serve as an effective placebo intervention in this trial.

**Trials registration:**

Chinese Clinical Trial Registry (identifier: ChiCTR-IOR-16008546; registration date: 27 May 2016).

## Background

Dysmenorrhea is a common disease in females of reproductive age [1], leading to the activity limitation, efficiency impairment, and even life quality decrease. Moreover, the vast majority is primary dysmenorrhea (PD), defined as painful menses in women with normal pelvic anatomy. Due to the lack of standard methods for assessing the severity of dysmenorrhea, studies based on the different definitions of the condition have reported the prevalence of PD as between 45% and 95% of menstruating women [2]. PD has negative impact on physical and psychological aspects of health, and its harm to the health will in turn aggravate the symptoms of PD, which is a vicious cycle. It has become an important research field to alleviate the symptom of PD safely and to improve the quality of life and well-being rating of female.

Therapeutically, the conventional pharmacotherapy for the PD is the use of non-steroidal anti-inflammatory drugs (NSAIDs) and oral contraceptives [3, 4]. Although NSAIDs and other drugs can alleviate the pain of PD significantly, their application is limited, mostly because of their disability in curing the disease ultimately, along with their side effects and unaffordable high prices [5, 6].

[name] and his colleagues from Changhai Hospital of Second Military Medical University, Shanghai, China invented and developed wrist-ankle acupuncture (WAA), a modern subcutaneous acupuncture technique, in the 1970s [7]. WAA which does not produce any pain or “needling sensation” is quite distinguished from the traditional acupuncture [8]. According to its unique theoretical system and the clinical evidence, WAA has demonstrated analgesic effects for both chronic and acute pain [9–11]. In addition, the active principle is considered to have correlation with the threshold of pain, or the regulation function of central nervous system, which is partly consistent with the analgesic mechanism of the traditional acupuncture [12–16]. There is a guaranteed guiding significance of WAA for PD’s treatment. To date, there are few studies investigating the application of WAA in the alleviation of PD. The present study is aimed at investigating the immediate analgesia effects of WAA for young females with PD.

## Methods/design

### Objectives

The aims of this study are to:observe the immediate analgesia effect of WAA in PD of young females;provide high-quality evidence-based recommendations on further treatment.

### Hypothesis

WAA therapy would relieve the pain of patients more effectively than sham acupuncture.

### Study design

The randomized parallel controlled single-blind trial was designed to observe the immediate analgesia effect of wrist-ankle acupuncture in primary dysmenorrhea of young females (Fig. 1). The study will be conducted in Changhai hospital of China from September 2016 to September 2017.

**Fig. 1 Fig1:**
[figure not shown]
Flowchart of the study design

### Participants and recruitment

Posters of this trial will be put on notice boards to recruit potential participants in the hospital. And the trial information leaflets will be distributed to the patients. The protocol details are explained to the participants in the leaflets and posts. Participants will be included only if they meet the inclusion criteria and provide written informed consent.

### Key inclusion and exclusion criteria

#### Inclusion criteria

patients conformed to the diagnostic criterion of PD according to the Primary Dysmenorrhea Consensus Guidelines [17];nulliparous women of 18 to 30 years old;instant pre-treatment VAS score of over 40 mm;no experience with treatment of WAA;signature of informed consent form.

#### Exclusion criteria

secondary dysmenorrhea caused by endometriosis, uterine myoma, endometrial polyps, pelvic inflammatory disease, or other gynecological problems confirmed by a gynecological abdominal ultrasound B examination;females with irregular/infrequent menstrual cycles (outside of the typical range 21 to 35 days’ cycle);patients complicated with severe diseases (e.g. cerebral, liver, kidney, or hematopoietic system diseases), or mental defects;take analgesic during the past 12 h;received other alternative therapies such as massage, acupressure, herbal therapy in the previous three months;poor treatment compliance (e.g. unstable working and living situation, difficult follow-up).

### Data collection

Two identical scale questionnaires should be completed before and after the treatment for assessing the pain-based symptoms of PD in the current menstrual cycle. Participants will complete the first questionnaire 10 min before the treatment, while the second one will be collected immediately after the treatment. The researchers will be present when the questionnaires are completed to ensure the reliability and validity.

### Interventions

According to the theory of WAA, each side of the body and each limb are longitudinally divided into six zones and one needling point is defined in each zone at the wrist or ankle. Needling the certain point will relieve the pain on the corresponding zone of the point. If the pain is on the upper (lower) part of the body (with the diaphragm as the demarcation), the needling point at the ipsilateral wrist (ankle) is selected [7, 18]. The pain sites of PD patients in the study are primarily located in the lower abdomen. To standardize the selection of the needling site and the treatment protocol, point 1 at both ankles will be needled (Fig. 2). Participants will be randomly assigned to the WAA group or the sham acupuncture group. The intervention will be applied during the first 24 h of the most intense dysmenorrhea’s occurrence. A single registered acupuncturist, with at least one year of previous WAA experience, will administer the care to all subjects.

**Fig. 2 Fig2:**
[figure not shown]
WAA needling point 1 on the ankle zone (Point lower 1) after insertion. The location of Point lower 1 is close to the medial border of tendo calcaneus

#### WAA group

WAA was administered on point 1 at both ankles on the first day when the pain occurs during the period. Retain the needle for 30 min. The subjects were asked to wear an eye mask. A disposable sterile WAA needle (0.25 mm in diameter and 25 mm in length, Suzhou Medical Appliance Factory, Jiangsu Province, China) was chosen in this trial. The target point was disinfected with an iodophordis infectant (Shanghai Likang Disinfectant Hi-tech Co. Ltd.). The processed needles were also held with thumb, index finger, and middle finger of the right hand. The skin near the target point was gently pressed with the left thumb to make it slightly taut. Then, the needle tip was swiftly inserted into the skin at the target point at an angle of 30°. The needle was lowered to the horizontal position and slowly advanced until the entire needle (except the handle) entered the subcutaneous tissue. The handle was then fixed to the skin with an adhesive tape. The needles were retained in the subcutaneous tissue for 30 min. Upon withdrawal of the needle, dry sterilized cotton balls will be firmly applied to the insertion points. The patient will only feel a negligible stabbing pain when the tip of the needle pierces the skin.

#### Sham acupuncture group

Sham acupuncture was administered on point 1 at both ankles on the first day when the pain occurs during the period. Retain the needle for 30 min. The subjects were asked to wear an eye mask. The target site was also disinfected with an iodophordis infectant (Shanghai Likang Disinfectant Hi-tech Co. Ltd.). The tip and most body of the disposable sterile acupuncture needle will be cut off and blunted (0.25 mm in diameter and 25 mm in length, Suzhou Medical Appliance Factory, Jiangsu Province, China) (Fig. 3). This sham needle has been successfully used in the previous trail design [19]. Only 2-3 mm of the needle body in length was remained. The processed needles were also held with three right-hand fingers (thumb, index finger, and middle finger). The skin near the target site was gently pressed with the left thumb to make it slightly taut. The needle tip was swiftly punctured the skin at the target point at an angle of 30° (The tip actually was not inserted into the skin). Then, the needles remained in the point of skin horizontally for 30 min. The handle was also fixed to the skin with an adhesive tape. For a successful sham treatment, the patient will also only feel a little negligible stabbing pain when the tip of the needle pierces the skin, and no other needling sensation.

**Fig. 3 Fig3:**
[figure not shown]
WAA needle & Sham acupuncture needle. WAA needle is the disposable sterile needle (0.25 mm in diameter and 25 mm in length, Suzhou Medical Appliance Factory, Jiangsu Province, China), sham acupuncture needle is also used the same model needle (0.25 mm in diameter and 25 mm in length, Suzhou Medical Appliance Factory, Jiangsu Province, China), while the tip and most body was cut off and blunted with only 2-3 mm of the needle body remained

### Randomization and blinding

An outside researcher who is not allowed to directly contact with the participants will perform computerized randomization. The assessor will also be blinded to the treatment allocation. The acupuncturist performing the WAA intervention and sham WAA intervention can’t be completely blinded, but he is not allowed to reveal any information about treatment procedures and outcomes to the participants or the assessor. Thus, both the participants and the assessor won’t distinguish clearly which intervention was given. A sealed envelope containing allocation sequence number for each participant will be opened after each participant is confirmed to meet the eligibility criteria and informed consent is made. If any error or disclosure with regard to randomization occurs, a new randomization sequence will be generated starting from the problematic serial number and applied to the participant from then on.

### Outcome measures

#### The primary outcome

Simple form of McGill pain questionnaire (SF-MPQ):

The SF-MPQ consists of 3 parts, including the Visual Analogue Scales (VAS), Present Pain Intensity scale (PPI) and Pain Rate Index (PRI). The main component is composed of 15 descriptors, including 11 sensory and 4 affective, and the descriptors are rated on an intensity scale (0 = none, 1 = mild, 2 = moderate or 3 = severe).

#### Secondary outcomes

The COX menstrual symptom scale (CMSS) will be rated as the main secondary outcomes. The CMSS consists of 18 items and each item has 5 grades according to symptom severity, including the evaluation on general frequency of menstrual symptoms and average severity. 0 point for absence of discomfort; 1 point for mild discomfort; 2 points for moderate discomfort; 3 points for severe discomfort; and 4 points for extremely severe.

Expectation and treatment credibility scale (ETCS), safety assessment, participants’ feeling of acupuncture questionnaire will also be included.

#### Sample size calculation

The sample size was determined according to the results of our previous pilot study, a two-arm design with WAA group and sham acupuncture group (the response rate was approximately 80% and 40%, respectively, showed by the pilot study). On the basis of the calculation performed by PASS11 with a two-sided significance level of 0.05 and power of 0.80, a total sample size of 52 would be required, with 26 for each group. Considering a maximum dropout tolerance of 15%, 30 initial participants in each group are required for this trial.

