### Statistical analysis

SPSS15.0 statistical software packages will be used to analyze the data. The statistician is blinded from the allocation of groups. For quantitative data, the distribution pattern and homogeneity of variance will be examined. If there is a symmetric distribution, the mean (M) ± standard deviation will be used for statistical description. Both paired samples t-test between the quantitative indices before and after treatment in one group and independent t-tests between the two groups will be used to determine and compare the effect of acupuncture. The entire statistical test will use bilateral examination, and the significance level sets at *P* < 0.05.

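### The sample size and its 80% power are for a comparison of response rates, but the stated primary analysis is a t-test on SF-MPQ scores, so the power figure does not describe that analysis

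*Protocol article*

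**What the plan says.** Protocol article, Sample size calculation: the planning inputs are pilot response rates ("the response rate was approximately 80% and 40%, respectively, showed by the pilot study"), with "a two-sided significance level of 0.05 and power of 0.80". The result is "a total sample size of 52 would be required, with 26 for each group", raised for dropout to 30 recruited per group. Response is not defined: no scale, cut-off or time point is given.

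Protocol article, The primary outcome: this is the SF-MPQ. "The SF-MPQ consists of 3 parts, including the Visual Analogue Scales (VAS), Present Pain Intensity scale (PPI) and Pain Rate Index (PRI". These are scores. No responder threshold is set on any of them, and none is singled out as the primary measure.

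Protocol article, Secondary outcomes: "The COX menstrual symptom scale (CMSS) will be rated as the main secondary outcomes". The CMSS is an item-score scale. The others are the expectation and credibility scale, safety, and the questionnaire on the feeling of acupuncture. None is described as a response rate.

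Protocol article, Statistical analysis: for quantitative data, paired t-tests within each group, and "independent t-tests between the two groups will be used to determine and compare the effect of acupuncture". No comparison of proportions is named.

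**The concern.** A power statement belongs to one endpoint, one test and one assumed effect. Here the power is computed for a difference in proportions, while the primary outcome and the between-group test concern means. Nothing in the article connects the two: response is not tied to an SF-MPQ component, and no SF-MPQ mean difference or SD appears anywhere.

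What is at stake is the planning rationale. A reader will take 80% as the chance of detecting a worthwhile SF-MPQ difference, but the article never says what difference that is. The size of effect for which 60 participants are enough is therefore unknown to anyone judging the design.

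**Working it through.** **Inputs from Sample size calculation.** Response rates 0.80 and 0.40; two-sided alpha 0.05; power 0.80; 26 evaluable and 30 recruited per group. Equal allocation is confirmed in the abstract ("30 patients for each group").

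**Step 1: reproduce the plan's own figure as a two-proportion design.** The mean proportion is (0.80 + 0.40)/2 = 0.60 and the difference is 0.40.

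- Pooled normal approximation: n = [1.960 × √(2 × 0.60 × 0.40) + 0.842 × √(0.80 × 0.20 + 0.40 × 0.60)]² / 0.40² = [1.358 + 0.532]² / 0.16 = 22.3, so 23 per group.
- With continuity correction: n′ = (n/4) × [1 + √(1 + 4/(n × 0.40))]² = 27.1, so 28 per group.
- Exact power of Fisher's test, summing binomial probabilities over all tables with p ≤ 0.05: 0.788 at 25, 0.799 at 26 and 0.802 at 27 per group.

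The stated 26 per group fits Fisher's exact test to within rounding. Strictly, 27 is the first of these sizes to reach 0.80, and the article does not say which PASS procedure was used. Still, 26 lies where a two-proportion calculation puts it, and 0.80 is about the power of that comparison.

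**Step 2: power of the test that is named.** For a two-sample t-test with n per group and a true difference of d standard deviations, the noncentrality parameter is d × √(n/2) with 2n − 2 degrees of freedom. For example, n = 26 and d = 0.5 give 0.5 × √13 = 1.80 on 50 df. The article supplies no d, so the values below are assumptions that show the range.

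| Assumed d (SD) | Power, 26 per group | Power, 30 per group |
|---|---|---|
| 0.4 | 29% | 33% |
| 0.5 | 42% | 48% |
| 0.6 | 56% | 63% |
| 0.7 | 70% | 76% |
| 0.8 | 81% | 86% |
| 1.0 | 94% | 97% |

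Solving for 80% power gives d = 0.79 with 26 per group and d = 0.74 with 30 per group.

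**Step 3: can the response rates be turned into a d?** Only with an added assumption. If response is a cut on the same score that the t-test compares, and that score is normal with equal SDs, then d = Φ⁻¹(0.80) − Φ⁻¹(0.40) = 0.842 + 0.253 = 1.09. At 26 per group the t-test would then have about 97% power.

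So the t-test's power is 80% only if the true difference happens to be close to 0.79 SD. The response rates do not lead to that value, even under the most natural link between them and the score.

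**The case against.** The strongest reply is that this is a condensed article. The Statistical analysis section limits its tests to quantitative data and is silent on categorical data, so a responder definition and its test may sit in the full protocol or analysis plan. That is possible, and it rules out saying that no responder analysis will ever be done. If response is indeed the intended primary endpoint, 80% is about right for it. But the point does not rest on an omission: the article states a primary outcome, its tests and a basis for the sample size, and these do not match.

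A second reply is that planning on a dichotomised score and then analysing the full score is conservative. This holds if response is a cut on the score being tested, as Step 3 shows. The article does not say that it is.

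A reader might also infer more than the document supports:

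- **That the trial is underpowered.** The direction of the discrepancy is unknown. The lower powers in the table rest on assumed effects, none taken from the article.
- **That a null result could not be interpreted.** It can be read from the estimate and its confidence interval, whatever was assumed at planning.
- **That a favourable cut-off would be chosen after the data are seen.** The article announces no responder analysis, so this is speculation.

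**Conclusion.** The mismatch stands. The 80% power is approximately that of a test of 80% against 40% responders, and it does not describe the SF-MPQ t-test, which is the only between-group test stated. The arithmetic for the 26 per group is acceptable for its own inputs; the fault is that those inputs concern an endpoint the article does not list.

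The consequence is an unknown power for the stated primary analysis, not a demonstrated shortfall. At 26 evaluable per group it runs from 42% at an assumed 0.5 SD to about 97% at 1.09 SD, the latter assuming a normal score, equal SDs and a cut on that same score. The design has 80% power at 0.79 SD. The mismatch alters neither the type I error nor the estimates of the listed analysis.

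**What to change.** Keep N=60 and make one of two changes.

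(a) If SF-MPQ scores are the intended primary endpoint, name one component as primary and say whether the groups are compared on the post-treatment value or on the change; the article settles neither. Then restate the power: 26 evaluable per group gives 80% power, two-sided 5%, for a difference of 0.79 SD. Convert this to scale units with the pilot SD of that quantity, which the article does not report. With N fixed, this states what the design can detect; it does not derive N afresh.

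(b) If response is the intended primary endpoint, define it now on a named SF-MPQ component with a fixed cut-off, list it as primary, and plan a test of proportions. With Fisher's exact test, power is about 0.80 at 26 per group for the stated rates.

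Either change is to protocol wording only and needs no extra participants. The downside is that the detectable effect becomes visible and may look less favourable than the present text suggests.

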### Statistical analysis

SPSS15.0 statistical software packages will be used to analyze the data. The statistician is blinded from the allocation of groups. For quantitative data, the distribution pattern and homogeneity of variance will be examined. If there is a symmetric distribution, the mean (M) ± standard deviation will be used for statistical description. Both paired samples t-test between the quantitative indices before and after treatment in one group and independent t-tests between the two groups will be used to determine and compare the effect of acupuncture. The entire statistical test will use bilateral examination, and the significance level sets at *P* < 0.05.

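### The between-group t-tests leave the pre-treatment score unadjusted and do not say whether post-treatment or change scores are compared; ANCOVA would settle this and, unless the pre-post correlation is near zero, add precision

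*Protocol article*

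**What the plan says.** The Statistical analysis section of the protocol article plans two kinds of test for quantitative outcomes. Within an arm it plans a "paired samples t-test between the quantitative indices before and after treatment in one group". Between arms, "independent t-tests between the two groups will be used to determine and compare the effect of acupuncture". No covariate is named, and the between-arm sentence does not say which quantity is compared.

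The Data collection section describes two identical questionnaires on pain-related symptoms: "Participants will complete the first questionnaire 10 min before the treatment, while the second one will be collected immediately after the treatment". I read these as containing SF-MPQ, the primary outcome, so each participant has a pre-treatment value of the score that is later compared.

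The trial is small. The abstract gives "30 patients for each group", and the Sample size calculation section allows for "a total sample size of 52 would be required, with 26 for each group" before dropout.

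**The concern.** A pre-treatment value of the outcome is often a useful predictor of the post-treatment value. A t-test on post-treatment scores discards it. A t-test on change scores uses it, but fixes the slope at 1 whatever the data show, which adds noise when the true slope is lower. ANCOVA estimates the slope.

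Two things are at stake. One is precision, in a trial that expects about 26 evaluable participants per arm. The other is that post-score and change-score t-tests can give different estimates and P values on the same data. The article settles on the t-test without saying which score it is applied to, so two candidate primary results remain open.

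**Working it through.** **The plan's own figure.** The inputs, all from the Sample size calculation section, are that "the response rate was approximately 80% and 40%, respectively", with a "two-sided significance level of 0.05 and power of 0.80". Exact enumeration of Fisher's test for 80% against 40% gives power 0.799 at 26 per arm and 0.802 at 27, so the stated 26 per arm reproduces within rounding. The dropout step, 26 × 1.15 = 29.9, gives the stated 30. This point does not dispute the sample size. That calculation concerns a binary response, so it supplies no mean difference, SD or correlation for the t-test.

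**Assumptions needed.** These are a common SD of 1 before and after treatment, a true difference of 0.6 SD, and a pre-post correlation r between 0 and 0.7. None of them is in the article.

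**Formulas**, with n = 26 per arm and two-sided 0.05:

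- Post-score t-test: variance 1, df = 2n − 2 = 50.
- Change-score t-test: variance 2(1 − r), df = 50.
- ANCOVA: variance (1 − r²) × (1 + 1/(2n − 4)) = (1 − r²) × 1.0208, df = 2n − 3 = 49. The factor 1.0208 is the price of estimating the slope.
- Noncentrality = 0.6 / (SD × √(2/26)), with √(2/26) = 0.2774; power from the noncentral t distribution.

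**Example at r = 0.5.**

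- Post score: 0.6 / 0.2774 = 2.163, power 56.4%.
- Change score: variance 2 × 0.5 = 1, so also 56.4%.
- ANCOVA: variance 0.75 × 1.0208 = 0.766, SD 0.875, noncentrality 2.472, power 67.9%.

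| r | Post-score t-test | Change-score t-test | ANCOVA |
|---|---|---|---|
| 0 | 56.4% | 32.3% | 55.5% |
| 0.1 | 56.4% | 35.3% | 56.0% |
| 0.2 | 56.4% | 38.9% | 57.2% |
| 0.3 | 56.4% | 43.4% | 59.5% |
| 0.5 | 56.4% | 56.4% | 67.9% |
| 0.7 | 56.4% | 78.2% | 83.6% |

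**Sensitivity to the assumed effect.** Take instead the difference at which the post-score t-test has 80.0% power at 26 per arm, which is 0.79 SD. ANCOVA then has 79.2%, 79.6%, 80.8%, 82.8%, 89.3% and 97.3% for r = 0, 0.1, 0.2, 0.3, 0.5 and 0.7. The change-score t-test has 65.8%, 80.0% and 95.1% for r = 0.3, 0.5 and 0.7. The pattern is the same.

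**In participants.** Against post scores, ANCOVA needs roughly n(1 − r²) per arm for the same precision. At r = 0.5 that is 26 × 0.75 = 19.5 instead of 26.

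**The case against.** The strongest reply is that nothing here is invalid. Under 1:1 randomisation an independent t-test, on post or change scores, is unbiased and controls the type I error. Chance baseline imbalance is already reflected in its standard error. All of this stands, and a reader who inferred from this point that the planned test is biased would be going beyond the documents.

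A reader might also infer that ANCOVA brings more power at no cost. The article does not support that. It gives no correlation, and at r of 0 to 0.1 ANCOVA is worse than the post-score t-test by up to 0.9 point (56.4% against 55.5% at r = 0). It spends one degree of freedom and assumes a linear relation to baseline. The entry rule of a pre-treatment VAS over 40 mm truncates the baseline of one SF-MPQ part, which makes a low correlation somewhat more likely for that part. If change scores are meant, the gain at r = 0.7 is only about 5 points at 0.6 SD (83.6% against 78.2%) and about 2 points at 0.79 SD.

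Nor does the 56% show that the trial falls short of its stated power. The 0.6 SD is an assumption of this check, and the stated 0.80 refers to response rates.

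Finally, covariates and the exact form of a score are often left to a full protocol or analysis plan that is not shown. That would answer a complaint about silence. Here, however, the article states the between-group test, and the point concerns that stated choice.

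**Conclusion.** The point holds as a recommended improvement in efficiency and clarity, not as an error of validity. The stated between-group test makes poor use of a baseline that is already collected, and it leaves the compared score undefined.

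Under the assumed 0.6 SD and 26 per arm, the gain over a post-score t-test is about 1 point at r = 0.2, 3 at r = 0.3, 11 to 12 at r = 0.5 and 27 at r = 0.7. The gain over a change-score t-test runs from about 21 points at r = 0.1 down to 5 at r = 0.7. The worst case in the range is a loss of less than 1 point against post scores. The sizes depend on a correlation and a standardised effect that the article does not give. The ordering at r of 0.2 and above does not change between the two effect sizes tried.

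**What to change.** In the Statistical analysis section, make the between-group analysis of SF-MPQ an ANCOVA of the post-treatment score on treatment group, with the pre-treatment score as covariate. Report the adjusted mean difference with its 95% CI and two-sided P value. Use the same model for CMSS and for any other score measured both before and after treatment. Do not extend it to measures without a stated pre-treatment value, such as the questionnaire on the feeling of acupuncture given at the end of treatment. If the t-test is kept, state whether it compares post-treatment or change scores.

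The cost is a change of wording, best made before anyone sees outcomes by group. It needs no extra data, visits or participants, and the model runs in the SPSS package already named. The statistical price is one degree of freedom, the linearity assumption, and the small power loss if the correlation proves to be near zero.
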